## Abstract

**Abstract:**

The main aim of this study is to compare the use of non-invasive ventilation (NIV) via helmet versus face mask where different interfaces and masks can apply NIV. However, some of the limitations of the NIV face mask were air leak, face mask intolerance, and requirement of high positive end expiratory pressure, which could be resolved with the use of the helmet NIV. NIV facemask will be applied as per the facial contour of the patient. NIV helmet is a transparent hood and size will be measured as per the head size. Both groups will have a standard protocol for titration of NIV.

Patients aged more than 18 years old and diagnosed with acute respiratory distress syndrome as per Berlin definition will be enrolled in the study after signing the informed consent. Subjects who met the inclusion criteria will receive 1 of the 2 interventions; blood gases, oxygenation status [Po2/Fio2] will be monitored in both groups. The time of intubation will be the main comparison factor among the 2 groups. The primary and secondary outcomes will be measured by the number of patients requiring endotracheal intubation after application of helmet device, Improvement of oxygenation defined as PaO2/FiO2 ≥ 200 or increase from baseline by 100, duration of mechanical ventilation via an endotracheal tube, intensive care unit length of stay, death from any cause during hospitalization at the time of enrolment, need for proning during the hospital stay, intensive care unit mortality, and the degree to which overt adverse effects of a drug can be tolerated by a patient including feeding tolerance.

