## Objectives

2

Primary objective: To assess the efficacy of non-invasive ventilation with HELMET in reducing endotracheal intubation rates in comparison with NIV face mask among patients with ARDS.

Secondary objective: to explore any improvement in oxygenation, time to intubation, ventilation days, and tolerance to HELMET NIV in comparison with facemask NIV.

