### Outcomes measures

4.4

Primary outcome measure:

1.Need for endotracheal intubation [ time frame: 6 weeks].Number of patients requiring endotracheal intubation after application of helmet device

Secondary outcome measures:

1.Improvement in oxygen saturation [time frame: 2 weeks]Improvement of oxygenation defined as “PaO2/FiO2 ≥ 200 or increase from baseline by 100”.2.Ventilator-free days [time frame: 28 days]Duration of mechanical ventilation via endotracheal tube.3.Intensive care unit length of stay [time frame: 4 weeks]The number of days admitted to the intensive care unit.4.Overall mortality [time frame: 90 days]Death from any cause during hospitalization at the time of enrollment.5.Need for proning [time frame: up to 24 weeks]Need for proning during the hospital stay.6.ICU mortality [time frame: 28 days]Death from any cause during ICU hospitalization at the time of enrollment.7.Patient tolerability [time frame: 28 days from randomization]The degree to which overt adverse effects of a drug can be tolerated by a patient, including feeding tolerance.

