### Type and classification of study- randomized control trial

5.1

*Intervention* – application of NIV by HELMET after randomizing the selected patients with odd and even numbers.

*Control group-* application of NIV with face mask after randomizing the selected patients with ARDS caused by COVID-19 and other pneumonia, type 1 and type 2 respiratory failure, Conscious and alert patients. NIV facemask will be applied as per the facial contour of the patient. NIV helmet is a transparent hood and size will be measured as per the head size. Both groups will have a standard protocol for titration if NIV. First, PEEP will be increased gradually to target spo2 above 90% with a Fio2 of 60% or less. Pressure support or IPAP will be increased slowly by 2 to 3 cm H2O to target a respiratory rate less than 30/min. The patient will be connected to non-invasive ventilation for 4 hours and will be on a high-flow nasal cannula for 1 hour. This 4:1 ratio will be continued till his condition improves or he will get intubated if he is worsening on non-invasive ventilation. Blood gases, oxygenation status [Po2/Fio2] will be monitored in both groups. The time of intubation will be the main comparison factor among the 2 groups. The intubation criteria will be the same for 2 groups which include, Worsening P/F ratio worsening acidosis, hemodynamic instability, poor neurological status.

The decision for intubation will be decided by the primary physician on duty

The intubated patient will be ventilated with lung-protective ventilation as per ARDS protocol.

If a patient in the control group is not tolerating the mask, they will be given the helmet in the other group as rescue therapy.

The weaning criteria will be the same for both groups and patients will be weaned to a high-flow nasal cannula or non-rebreathing mask. For weaning, pressure support and PEEP will be reduced gradually and will be discontinued if the respiratory rate is less than 30/min and P/F ratio more than 150 with a PEEP of 5 cm H20. If 1 patient is out of NIV for more than 12 hours a day for 48 hours, that will be considered as weaning.

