### Data monitoring & auditing

6.1

The clinical trial master file will be kept along with informed consent from the patients according to the Joint Commission International, Medical Research Center (MRC), and the Ministry of Public Health (MoPH) requirements.

Any side effects or adverse events related to the trial will be reported to the hospital research committee and MRC.

A regular registration report will be generated to monitor patient accrual and completeness of registration data. A routine data quality report will be generated to assess missing data and inconsistencies. Accrual rate and extent and accuracy of evaluations and follow-up will be monitored periodically throughout the study period, and potential problems will be brought to the attention of the study team for discussion and action. Random-template data quality and protocol compliance audits may be conducted by the study team, at a minimum of once per year or more frequently if indicated. Data safety and monitoring will be conducted according to the HMC-IRB, Ethics, and Data Safety Monitoring Board regulations.

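### Secondary outcome 7 defines tolerability as tolerance of a drug's adverse effects, although the trial compares two ventilation interfaces; apart from feeding tolerance, it does not measure interface tolerance

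*Protocol article*

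**What the plan says.** Section 2 (Objectives) of the protocol article gives one secondary objective, exploratory in wording. Its four parts are oxygenation, time to intubation, ventilation days, and "tolerance to HELMET NIV in comparison with facemask NIV".

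Section 4.4 (Outcomes measures) lists seven secondary outcomes. The seventh is headed "Patient tolerability [time frame: 28 days from randomization" and is defined as "The degree to which overt adverse effects of a drug can be tolerated by a patient, including feeding tolerance". The abstract carries the same definition: "the degree to which overt adverse effects of a drug can be tolerated by a patient including feeding tolerance".

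Section 5.1 describes the two arms as "application of NIV by HELMET after randomizing the selected patients with odd and even numbers" and "application of NIV with face mask after randomizing the selected patients with ARDS". It also contains a rescue step that begins "If a patient in the control group is not tolerating the mask", under which such a patient is given the helmet. No corresponding step is stated for helmet patients.

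**The concern.** The objective asks about tolerance of two devices, and the outcome that should answer it speaks of a drug. Concomitant medicines are not what is randomised. A difference in how patients bear their side effects would say little about helmet against mask.

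Tolerance is part of the case for the trial. The introduction lists intolerance among the limitations of the face mask and describes the helmet as better tolerated. Mask intolerance is also the event that moves control patients to the helmet, yet no listed outcome counts it. The study is open-label (section 3), so a subjective outcome with an unsuitable definition could be given its working meaning after the data have been seen.

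**Working it through.** The point rests on no rate, error level or sample size, so there is no figure in the plan to reproduce. The check is a comparison of sections.

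1. **What is randomised.** Section 5.1: helmet NIV or face mask NIV. No study drug appears anywhere in the article.
2. **What is asked.** Section 2: tolerance of one interface compared with the other.
3. **What outcome 7 measures as written.** It has two elements. The first, tolerance of a drug's adverse effects, does not refer to the randomised interface. The second, feeding tolerance, can be compared between the arms.
4. **Whether another outcome fills the gap.** The primary outcome is intubation. Secondary outcomes 1 to 6 are oxygenation, ventilator-free days, ICU stay, overall mortality, need for proning and ICU mortality. None measures discomfort with, refusal of, or a switch from the assigned interface.
5. **Whether it is an isolated slip.** The drug wording stands in both the abstract and section 4.4, so both need the change.
6. **Extent.** One of seven secondary outcomes, and one of four parts of the secondary objective.

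Two features of section 5.1 limit how the outcome can be redefined.

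- *One-way switch.* A switch for intolerance is stated only for mask patients. Suppose a proportion p of patients in each arm is truly intolerant, every intolerant mask patient is switched, and no helmet patient is. A count of switches then gives p in the mask arm and 0 in the helmet arm. The apparent difference is p − 0 = p in favour of the helmet, although the interfaces are equally tolerated.
- *Scheduled breaks.* NIV runs for 4 hours, followed by 1 hour on high-flow nasal cannula. One cycle is 4 + 1 = 5 hours, so a full day on the schedule contains 24 / 5 = 4.8 cycles. If any interruption counted as stopping the interface, every patient who completed one cycle would meet the endpoint.

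Intubation also ends use of the interface, so it must be kept apart from intolerance when it is done for respiratory worsening.

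**The case against.** The strongest reply is that no one would be misled. The outcome is titled patient tolerability, the objective says whose tolerance is meant, and no drug is under study. The likeliest explanation is a generic definition pasted in without editing, and trial staff would probably read it as referring to the interface. An article may also leave the scale or threshold to the full protocol.

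Much of this stands. It is unlikely that staff would score reactions to medicines, and the absence of a scale is no finding here. But the printed definition is wrong, not merely brief. Reading the interface in place of the drug still leaves open how a mask patient given the helmet is classified.

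A reader might infer that the tolerance objective has no usable endpoint at all, or that a whole secondary objective is lost. The documents do not support either: feeding tolerance remains comparable between arms, and tolerance is one part of four.

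A reader might also take the sentence in section 6.1, "Any side effects or adverse events related to the trial will be reported", as evidence that adverse events are handled inadequately. It does not show that. The same section places safety monitoring under institutional review, ethics and data safety monitoring board rules, and an article commonly leaves adverse-event collection to the full protocol.

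**Conclusion.** The point holds in a limited form. The definition of secondary outcome 7, in section 4.4 and in the abstract, does not match the intervention or the tolerance part of the objective. Apart from feeding tolerance, it does not measure what section 2 asks. As written, the trial is poorly specified to compare interface tolerance, which falls short of saying that it cannot do so. The primary outcome and the other six secondary outcomes are unaffected.

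This rests on the article alone and assumes that the full protocol does not define the outcome differently. If it does, the article still needs to be brought into line with it.

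**What to change.** In section 4.4 and in the abstract, replace the drug wording with tolerance of the randomised interface within 28 days of randomisation, analysed by randomised arm. Then state that:

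- intolerance is recorded by one criterion, applied identically in both arms whether or not a switch of interface is available;
- feeding tolerance is kept as a component and recorded in the same way in both arms;
- a mask patient moved to the helmet because of intolerance counts as mask-intolerant and stays in the face mask arm for analysis;
- the scheduled high-flow periods, and intubation for respiratory worsening, do not count as intolerance.

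This concerns measurement only and leaves the rescue step as it is.

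The cost is one revised definition in two places and one or two data fields. In the mask arm, intolerance already has to be recognised in order to apply the rescue step. In the helmet arm, nothing stated prompts its recognition, so parallel recording there is new work. Some subjectivity will remain because the trial is open-label. A common criterion reduces it but does not remove it.

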### Participant timeline

4.5

The expected time of the trial will be 1 calendar year after ethical approval and will be renewed annually for 5 years.

### Sample Size & Recruitment

4.6

Sixty patients will be recruited after randomizing the selected patients with odd or even numbers.

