## Trial design

3

This is a phase-III, randomized, comparative, parallel assignment, open-label clinical study

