### Study setting

4.1

The study will take place in the intensive care unit in Hazm Mebaireek General Hospital in Qatar. All included patients are diagnosed with ARDS, type 1, or type 2 respiratory failure, and they are conscious and alert. All the investigators on this protocol are from Hazm Mebaireek General Hospital. The details of the procedure and interventions are mentioned below in the background and methods sections.

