### Informed consent

7.3

The researcher will do screening from the patient pool; those patients found to be eligible as per inclusion and exclusion criteria will be interviewed to discuss the trial if accepted, they will be enrolled in the study the PI where the participant will be given free time to decide to participate or not the consenting process will start by screening then interviewing the eligible patient explaining about the trial rationale benefits risks and objectives his or her right to participate or not to participate without being affected and the right to withdraw at any time.

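### Allocation by odd or even number, with the source of the number unstated, reads as a predictable rule and leaves this open-label, single-centre trial exposed to selection bias in either direction

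*Protocol article*

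**What the plan says.** Allocation is described in two places in the protocol article, by the same rule.

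- Section 4.6 (Sample Size & Recruitment): "Sixty patients will be recruited after randomizing the selected patients with odd or even numbers".
- Section 5.1 (Type and classification of study): the intervention is "application of NIV by HELMET after randomizing the selected patients with odd and even numbers".

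Neither section says what the number is, who assigns it, or who can see it.

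The setting is fixed elsewhere. Section 3 (Trial design) calls the study a "randomized, comparative, parallel assignment, open-label clinical study". Section 4.1 (Study setting) places it in one hospital's ICU and adds: "All the investigators on this protocol are from Hazm Mebaireek General Hospital". Section 7.3 (Informed consent) states: "The researcher will do screening from the patient pool"; it goes on to say that "the consenting process will start by screening then interviewing the eligible patient".

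**The concern.** A two-arm rule based on odd or even numbers can mean two different things. It can mean the parity of a number the patient already carries or receives in order of arrival. That is quasi-random assignment, and whoever knows the number knows the arm. It can also mean the parity of digits on a random-number list, which is a legitimate way to make a 1:1 sequence if the list is concealed. The text does not say which, and its wording suggests the first.

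The distinction matters because several safeguards are absent by design. The trial is open-label. Recruitment sits with a research team at a single site. Two exclusions in section 4.3, haemodynamic instability and morbid obesity, carry no threshold and leave room for judgement. The Berlin definition admits PaO2/FiO2 values from 100 or below up to 300, so severity varies widely and can be seen before a patient is approached. The primary outcome in section 4.4 is intubation, which section 5.1 leaves to the physician on duty, so no blinded endpoint offsets an uneven intake.

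If a recruiter can foresee the arm, patients can be deferred or approached according to prognosis. The resulting difference in intubation is mixed with the device effect, and with 60 patients adjustment can repair it only in part.

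**Working it through.** No figure in the article bears on this point, so there is none to reproduce. The check has two parts.

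**1. What the text establishes**

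| Question | Where | Answer in the text |
|---|---|---|
| What determines the arm? | 4.6, 5.1 | Odd or even number |
| What is the source of the number? | 4.6, 5.1 | Not stated |
| When is the arm set? | 4.6 | Recruitment follows randomising |
| When does enrolment occur? | Abstract | After the consent form is signed |
| Who screens? | 7.3 | The researcher |
| Is the arm masked? | 3 | No |

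The order of events is not settled. Read literally, section 4.6 sets the arm before recruitment. The Abstract puts consent before enrolment and then has eligible patients receive one of the two interventions. Sections 4.6 and 5.1 both speak of randomising selected patients, which puts selection first.

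**2. How large the distortion could be**

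Inputs: 60 patients in total (4.6). The rest is assumed: 30 per arm, no true effect, a two-sided 5% test, half of all patients high-risk, and intubation risks of 65% (high-risk) and 15% (low-risk).

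Arm risk = share high × 0.65 + share low × 0.15.

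- Balanced: 0.5 × 0.65 + 0.5 × 0.15 = 40% in each arm.
- 60% high-risk: 0.6 × 0.65 + 0.4 × 0.15 = 45%.
- 40% high-risk: 0.4 × 0.65 + 0.6 × 0.15 = 35%.
- Spurious difference: 45% − 35% = 10 points.

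Rejection rates by exact enumeration depend on how the risk mix is treated:

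| Risk mix | Test | Balanced | 60% v 40% high-risk |
|---|---|---|---|
| Random (each patient drawn at the average risk) | Chi-square | 4.9% | 12.2% |
| Random | Fisher | 2.6% | 7.6% |
| Fixed (exactly 18 v 12 high-risk; 15 v 15 when balanced) | Chi-square | 2.2% | 8.5% |

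By symmetry the same rates apply whichever arm receives the sicker patients. Only the direction of the false result changes.

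A second model describes behaviour. A recruiter who knows the next arm passes over a share f of high-risk patients when the helmet is next, and a share f of low-risk patients when the mask is next. With half the patients high-risk, the high-risk shares become (1 − f)/(2 − f) in the helmet arm and 1/(2 − f) in the mask arm. For f = 25% these are 0.75/1.75 = 42.9% and 1/1.75 = 57.1%. With risks of 60% and 20% the arm risks are 37.1% and 42.9%, a difference of 5.7 points. The table gives the spurious difference in points, then the rate of false significant results favouring the helmet.

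| Assumed risks | f = 0 | f = 10% | f = 25% | f = 50% |
|---|---|---|---|---|
| 60% / 40% | 0; 2.6% | 1.1; 3.1% | 2.9; 4.2% | 6.7; 7.7% |
| 60% / 20% | 0; 2.4% | 2.1; 3.6% | 5.7; 6.4% | 13.3; 18.0% |
| 80% / 20% | 0; 2.6% | 3.2; 4.5% | 8.6; 10.0% | 20.0; 34.9% |

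The range runs from negligible to serious, and the article offers nothing to narrow it.

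**The case against.** The best defence is that foreseeability is inferred. Odd and even digits from a concealed random list would give a proper sequence, and the article does not exclude that. It is also a condensed account, and details of sequence generation and concealment may stand in the full protocol. Silence on concealment alone would not be a finding.

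That defence limits the point but does not remove it. The article does state a method, twice, and on its ordinary meaning the method is predictable.

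Three stronger readings are tempting, and the documents do not support them.

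- **The arm is known before the patient is approached, so the trial is not randomised.** The source of the number is not given, and the Abstract's order of consent and enrolment sits uneasily with section 4.6.
- **One unblinded team does everything, including reading the allocation.** Section 7.3 names the researcher for screening and refers to the principal investigator in an unclear clause. It does not say who holds or reads the number.
- **The rule would produce a false helmet benefit.** The Introduction states a hypothesis in favour of the helmet, but clinicians could equally steer the sickest patients towards it, which would bias against it.

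The magnitudes are also open to challenge, fairly. The risks and shares are assumed. An 18 v 12 split of 30 high-risk patients, or a more extreme one in either direction, arises by chance in about 20% of properly randomised trials of this size, so such an imbalance would not by itself show steering. What steering changes is that the imbalance becomes systematic.

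**Conclusion.** The point holds in this form: sections 4.6 and 5.1 fix an allocation rule that, on its natural reading, is predictable, in an open-label, single-centre trial where the researcher screens, interviews and starts consent. The next arm could be foreseen, and selection bias in either direction could distort the primary comparison.

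The size is illustrative only. In the worked example a 60% v 40% imbalance in high-risk patients gives a spurious 10 points, and chi-square rejection of roughly 8% (fixed mix) to 12% (random mix) with no true effect. This rests on assumed risks of 65% and 15%, 30 patients per arm and a two-sided 5% test. It is not an estimate of what will happen in this trial.

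A reader might infer that selection has occurred, or that the trial is certainly quasi-randomised. The text supports neither. Correction is still needed on either meaning of the rule: if the number is predictable the method must change, and if it comes from a concealed list the text must say so.

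**What to change.** Replace the odd/even rule in sections 4.6 and 5.1 with:

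- a computer-generated 1:1 sequence in randomly varying permuted blocks, prepared by the biostatistician mentioned in section 5.3 and held away from those who recruit;
- release of the arm only after eligibility is recorded and consent is signed, for example by sequentially numbered, opaque, sealed envelopes.

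Reword section 4.6 so that randomisation follows consent, in line with the Abstract. Stratification by baseline PaO2/FiO2 category is optional.

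If the odd and even numbers already come from a concealed random list, state that instead: how the list was made, who holds it, and when the arm is revealed.

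The cost is a protocol amendment and a few hours of the biostatistician's time. The sample size stays at 60, with no added procedures. The change protects only patients allocated after it takes effect.
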